### Interventions

The Web-based computer-tailored intervention and the Web-based peer support intervention followed a rigorous theory-based and evidence-based development process involving a literature review, focus groups with T2D patients, a usability testing phase, and multidisciplinary expertise. As outlined in the background section, both interventions are based on the I-Change Model, in which concepts borrowed from SDT and the MI approach are integrated as part of the theoretical framework (Figure 1). These concepts are as follows: (1) type of motivation (SDT-related); (2) importance ruler (MI-related); (3) confidence ruler (MI-related); and (4) MI-SDT concepts application. In short, feedback messages about the *type of motivation* aim to inform participants in both interventions that controlled or autonomous forms of motivation can influence the adoption and maintenance of regular PA [80]. *Importance ruler* and *confidence ruler* are used mainly to provide feedback to participants with MI-related strategies. The remaining added construct, *MI-SDT concepts application*, aims to provide messages to participants using a style of communication that is consistent with both SDT and MI across all of the interventions’ features.

**Figure 1 figure1:**
[figure not shown]
The theoretical framework of both interventions integrating the I-Change Model, Self-Determination Theory (SDT), and Motivational Interviewing (MI).

### Content Specific to the Computer-Tailored Intervention

A key component of the computer-tailored intervention is that it uses recent techniques borrowed from computer-tailoring research to provide messages in a personalized fashion to its participants [81,82]. Eight computer-tailored motivational sessions based on PA-related cognitions and current PA level were offered to participants. These sessions provided messages matching how individual participants scored on each cognitive construct and were complemented with personalization (eg, name) and different types of feedback (eg, descriptive, comparative, or evaluative) [81]. One motivational session per week was made available to participants over an 8-week period. The order in which each of these motivational sessions was offered in the intervention was established so as to fit the theoretical framework and its 3 related phases. First, motivational session 1 aimed to raise awareness among participants regarding how their insufficient PA level could impact their health (ie, tailored feedback on risk perception and current PA level). This corresponds to the first phase of our theoretical framework: increasing the importance of change in participants [83]. Next, all other sessions aimed to motivate participants toward increasing their PA level over the course of the intervention by providing them with tailored feedback related to their attitude, social influence, self-efficacy, type of motivation, and intention. This corresponds to the second phase of our theoretical framework, which was to develop participants’ motivation for making the desired change [84]. Moreover, all computer-tailored motivational sessions were built such that they ended by querying participants about their desire to build a PA action plan for the week, which aimed to help them take action, and thus, increase their PA level. For instance, if a participant told the software he wanted to build an action plan, he was redirected to the action planning tool available on the website to build his plan. This last step is in concordance with the final phase of our model, in which motivation is transferred into the adoption of the desired behavior [85]. To integrate SDT and MI within the computer-tailoring component, all motivational sessions were also interactively geared so that participants could develop an autonomous motivation to practice more PAs. Furthermore, all sessions used various techniques associated with MI and its basic interview skills: (1) asking open questions, (2) affirming, (3) reflecting, (4) summarizing, and (5) informing and advising [60] (see Multimedia Appendix 1) [86-88]. Finally, readers are encouraged to read Moreau et al [80] for an in-depth description of the algorithms behind the tailoring component of the intervention and examples of messages received by participants during computer-tailored motivational sessions.

### Content Specific to the Peer Support Intervention

A key component of the peer support intervention is that it provides opportunities for participants to support each other by using a Web-based discussion group. More precisely, the online peer support component can be viewed as a semi-guided private Facebook group moderated by a clinical nurse. At their convenience, participants had the opportunity to visit either the intervention website or to interact with other participants via the Facebook group during an 8-week intervention period. Participants randomized into the peer support intervention were exposed to the same content as participants in the computer-tailored intervention regarding PA-related cognitions. However, the peer support intervention was targeted, meaning that the same content was provided to all participants, regardless of their individual characteristics beyond being adults with T2D. For the first 4 weeks, participants received 2 web articles per week that provided information on PA-related topics (eg, risk perception, PA guidelines, attitude), which were made available directly on the website and posted simultaneously in the Facebook group. For weeks 5, 6, and 7, participants received 1 web article per week that provided information on other PA-related topics (eg, self-efficacy, intention, and action planning). No article was offered during the last week, allowing the nurse-moderator to discuss participants’ appreciation for the intervention through the Facebook group. Similar to the computer-tailored intervention, the order in which each web article was made available was established to correspond to the theoretical framework of the study. All topics in each web article are presented in Multimedia Appendix 2.

The clinical nurse moderated the group using a method we developed that integrates SDT concepts and MI techniques, aiming to encourage participants to focus their discussions on PA-related topics and develop their own reasons for practicing more moderate-intensity aerobic PAs [60] (see Multimedia Appendix 1). The following steps explain the method used by the moderator: (1) participants were first greeted by the nurse-moderator when they joined the Facebook group; (2) they were then invited to read the introductory text describing the underlying MI spirit sought for the group, which was accessible in the group’s description section; (3) when posting a new web article to the Facebook group’s page, the nurse-moderator always simultaneously posted 1-2 open-ended questions on the group’s wall that were related to the article topic (see Multimedia Appendix 3) and aimed to encourage participants to develop their own motivation; (4) 2 days after the questions were posted, the nurse-moderator summarized the answers posted by participants, with an emphasis on comments made in favor of adopting the desired behavior; (5) for the last 4 weeks of the intervention, since only 1 article was posted per week during this period (or no article during the last week), the nurse-moderator spent at least 1-2 hours per day, 3 days a week, replying to specific participants’ comments to show interest, encourage further self-exploration, and favor group participation [60]. Despite this standardized method adopted by the moderator, it is important to note that participants were part of a peer support intervention and most interactions in the group were between themselves. While participants had the opportunity to talk about the web articles posted on the Facebook group’s page, they could also discuss any topic or concern they wanted to share with other participants.

### Additional Features

Despite their distinct core content, both interventions possessed the following similar features: (1) the appearance of the website home page, (2) a tool for self-monitoring of PA behavior, (3) tools for goal setting and action planning, (4) tabs providing safety tips on how to practice PA properly, and (5) access to technical support via email. The designs of the websites were different except for the home page (see Multimedia Appendix 4), as they were developed by different web solution companies at different times during the study development phase. Additionally, other evidence-based behavior change techniques according to Michie et al’s taxonomy [89] were integrated into both interventions and can be viewed in detail in Multimedia Appendix 5 [90-96]. These were identified in the literature review preceding the development of both interventions [80]. Lastly, the computer-tailored and peer support interventions both started on 29 September 2014 and ended on 22 November 2014.

Table 1 presents a broad overview of the intervention components for each experimental condition. Multimedia Appendix 2 presents a more detailed overview of both interventions, including timelines.

**Table 1 table1:** Overview of components found in each intervention group and the control group

		Study groups		
		Computer-tailored intervention	Peer support intervention	Control group
**Computer tailoring**				
	Personalization^a^	x^b^		
	Content matching^a^	x^b^		
	Feedback^a^	x^b^		
Peer support opportunities			x^b^	
**PA: cognitions messages**				
	Intention	x	x	
	Attitude (pros and cons)	x	x	
	Social influence	x	x	
	Self-efficacy	x	x	
	Risk perception	x	x	
	Type of motivation	x	x	
Action planning		x	x	
Goal setting		x	x	
Self-monitoring of PA		x	x	
Periodic email prompts^c^		x	x	x

^a^Contemporary computer-tailoring terminology summarized by Harrington and Noar [81].

^b^Distinctive components of each intervention

^c^Emails were sent only to stimulate participants to reuse the interventions or to complete posttest evaluations.

### Control Group

Participants in this group did not participate in any intervention for the duration of the study. Following the last follow-up questionnaire, participants from this group were offered the fully automated, computer-tailored, Web-based intervention.

### Outcome Assessments

Emails were used to invite participants to complete baseline, 3-month, and 9-month follow-up questionnaires on the intervention websites. Participants were invited to complete their baseline questionnaire during the enrolment period between 2014 September 15 to 2014 September 18. Participants were invited to complete their 3-month and 9-month follow-up questionnaires during the period between 2014 December 16 and 2015 January 4 and during the period between 2015 June 5 and 2015 July 4, respectively. As it is well known that Internet interventions generally suffer from a high attrition rate [97], a financial incentive was offered to participants for completing the 3-month ($20) and 9-month ($10) follow-ups.

### Primary Outcomes

PA level was evaluated with an adapted version of the Godin Leisure Time Exercise Questionnaire (GLTEQ) [98,99]. An independent evaluation of this instrument indicated that it compared favorably in terms of reliability and validity to 9 other self-report measures of PA on test-retest methods, objective measure of PA, and fitness indexes [100]. The GLTEQ had a one-month test-retest reliability of .62 and concurrent validity coefficients of .32 with an accelerometer and .56 with maximum oxygen uptake [100]. Participants were asked (1) the frequency with which they practiced intensity-specific aerobic PAs (ie, low, moderate, vigorous) in a typical 7-day week and (2) the average duration in minutes of these activities for each intensity category. Final PA levels were obtained by calculating the converted total minutes per week of moderate-intensity aerobic PA that participants engaged in during a typical week; only moderate (4 metabolic equivalents [METS]) to vigorous (7.5 METS) types of aerobic PA were considered, and the total minutes of vigorous aerobic PA/week were considered as 1.875 × minutes of moderate aerobic PA/week (7.5 METS/4 METS = 1.875). Using this method, a participant was considered “regularly active” with a score greater than or equal to 600 METs-min/week. This threshold is the equivalent of 150 min of moderate-intensity aerobic PA per week and corresponds to the recommendations of the Canadian Diabetes Association [72].

### Secondary Outcomes

PA-related cognitions were also assessed to identify the mediating processes through which behavior change occurred in participants according to the answers they provided during the baseline, 3-month, and 9-month follow-up assessments on the study’s websites. The items used for the assessment of attitude, social influence, self-efficacy/perceived behavioral control, and intention were developed according to the guidelines from Ajzen's Theory of Planned Behavior [47] (Table 2). A test-retest procedure was conducted over a 2-week period with a subgroup of 29 individuals with T2D. The mean age of the participants was 57.3 years (SD 10.8), 48% (14/29) were male, and 45% (13/29) had completed postsecondary education. The Cronbach alpha coefficients and intraclass correlation coefficients are reported in Table 2. As for the items assessing the type of motivation of participants, a modified, validated, French-language version of the BREQ-2 [101] (Behavioural Regulation in Exercise Questionnaire, version 2) was used to measure all possible types of motivation a participant could experience, including integrated motivation, which is normally absent in the standard BREQ-2 [102]. The investigators who developed the questionnaire assessed the construct and discriminant validity with confirmatory factor analysis. Nomological and convergent validity were also assessed with correlation analysis. Questionnaire validation results are reported elsewhere [101].

**Table 2 table2:** Description of psychosocial variables and psychometric values.

Variable	Items	Scale	Internal consistency^ a ^	Test-retest reliability ^ c ^
Intention			.84	.45
	I intend to be regularly active in the next month.	Unlikely (+1)/likely (+7)		
	My plans are to practice physical activities regularly in the next month.	Disagree (+1)/agree (+7)		
	I estimate that my chances of practicing physical activities regularly over the next month are...	Weak (+1)/good (+7)		
Attitude			.58	.49
	I think that practicing physical activities regularly in the next month would be…	Bad (+1)/good (+7)		
		Useless (+1)/useful (+7)		
		Unenjoyable (+1)/enjoyable (+7)		
		Unpleasant (+1)/pleasant (+7)		
Self-efficacy			.83	.57
	I feel capable of practicing physical activities regularly in the next month.	Disagree (+1)/agree (+7)		
	For me, practicing physical activities regularly in the next month would be…	Difficult (+1)/easy (+7)		
	How much control do you feel you have over your ability to practice physical activities regularly?	No control (+1)/control (+7)		
Social influence (subjective norm)			.87^b^	.77
	People who are important to me would support me if I were to practice physical activities regularly in the next month.	Disagree (+1)/agree (+7)		
	People who are important to me think I should practice physical activities regularly in the next month.	Disagree (+1)/agree (+7)		
Social influence (descriptive norm) ^ d ^			—	—
	How many people who are part of your daily life (children, spouse/partner, physician, friends, colleagues, etc) are physically active on a regular basis?	Nobody (+1); a minority (+2); half (+3); a majority (+4); everybody (+5)		

^a^Internal consistency reported as Cronbach alpha coefficient for variables of 3 items or more.

^b^Internal consistency reported as Spearman’s correlation coefficient for variables of 2 items.

^c^Intraclass correlation coefficient.

^d^No data provided for descriptive norm, given the change of scale following the test-retest.

### Statistical Analysis

Descriptive statistics will be used to summarize the baseline characteristics of the participants for sociodemographic variables (ie, origin, occupation, gender, age, and education), anthropometric variables (ie, height, weight, and body mass index), psychosocial variables (ie, attitude, social influence, self-efficacy, type of motivation, and intention), and PA level. In line with the hypotheses, linear mixed model analyses for repeated measures will be used to examine the effectiveness of the computer-tailored intervention (H1) and peer support intervention (H2) relative to the control group and also to compare both interventions to each other (H3). A linear mixed-model approach is very well suited for modelling data containing repeated measures from several participants [103] and has the advantage of providing better capabilities for handling missing observations when data are missing at random, compared to more traditional approaches such as repeated measures analysis of variance [104,105]. In accordance with the statistical procedure and for each analysis, group, time, and time × group will be included as independent variables and minutes per week of moderate-intensity aerobic PA will be included as the dependent variable. Analyses will be adjusted for sociodemographic characteristics and other relevant variables that significantly differ between the 3 study arms at baseline. In the presence of statistically significant interaction terms, post-hoc tests will be applied to compare differences between all pairs of means. All pairwise tests of the computer-tailored or peer support interventions compared to the control group will be 1-tailed, and tests comparing both interventions together will be 2-tailed. Finally, potential mediators of the interventions’ effects will be explored. Based on the theoretical framework (Figure 1), a mediation analysis will be conducted involving a multicategorical independent variable (both interventions relative to control group), with type of motivation and intention as mediator variables in serial, and PA behavior as the dependent variable. Hayes and Preacher’s SPSS macro will be used for exploring the potential mediators [106]. The statistical analyses will be conducted with SPSS 22.0.

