### Aim of the Study and Hypotheses

The primary aim of this study is to evaluate the independent effectiveness of two Web-based interventions in promoting regular moderate-intensity aerobic PA among insufficiently active adult Canadian Francophones with T2D. In line with this aim, it is hypothesized that the Web-based computer-tailored intervention (H1) and the Web-based peer support intervention (H2) will be more effective at increasing moderate-intensity aerobic PA levels compared to a control group at 3 and 9 months after baseline. Another aim of this study is to compare the relative effectiveness of the two Web-based interventions at increasing moderate-intensity aerobic PA levels. Hence, the third hypothesis is that participants in both intervention groups will show a different level of moderate-intensity aerobic PA at 3 and 9 months after baseline. This hypothesis is formulated bilaterally, because no study to date has compared these two methods.

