### Sample Size Calculation

Calculation of the sample size was achieved with GPower 3.0.10, and instructions for selecting different criteria were taken from Erdfelder et al [73]. Thus, according to a mixed-plan, 3 (2 experimental groups and 1 control group) x 3 (baseline and 3- and 9-month follow-ups) design, assuming a statistical power of .80 and an alpha value of .05, a total sample size of 204 participants is necessary to detect a conservative effect size of d=.20 [74]. This effect size was chosen with reference to results observed in the field of computer-tailored interventions [33,75] and considering the modest evidence observed to date for Web-based interventions integrating online opportunities for peer support [25,76]. Moreover, to obtain the calculated sample size at the end of the study (N=204), it was estimated that at least 6000 participants needed to be solicited through the invitation emails sent by Diabète Québec. This estimate was based on a similar study [77], and a review of additional literature: (1) from the 6000 participants solicited, 30% (1800/6000) will agree to participate in the study [77,78]; (2) of this number, almost 100% (1800/1800) will have T2D, since preselection of potential participants with this type of diabetes will be executed by Diabète Québec; (3) 85% (1530/1800) will not have medical indications limiting the practice of moderate-intensity aerobic PA [79]; (4) 70% (1071/1530) will not meet the Canadian Diabetes Association guidelines related to aerobic PA [77]; (5) 70% (749/1071) will have access to the Internet [15]; and (6) 60% (449/749) will complete the study [77]. However, this algorithm has overestimated the number of participants enrolled at baseline, which was 234.

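### The three pre-stated hypotheses are tested only as post-hoc comparisons behind a significant time × group interaction, which costs power and gives weak error control

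*Protocol article*

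**What the plan says.** The Aim of the Study and Hypotheses section opens with "The primary aim of this study is to evaluate the independent effectiveness of two Web-based interventions". It sets out H1 and H2 as directional comparisons with control and H3 as a two-sided comparison between the interventions, all at 3 and 9 months.

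The Statistical Analysis section assigns these hypotheses to a linear mixed model in which "group, time, and time × group will be included as independent variables". The between-arm comparisons then follow under a condition: "In the presence of statistically significant interaction terms, post-hoc tests will be applied to compare differences between all pairs of means". On sidedness, the rule for H1 and H2 is that "All pairwise tests of the computer-tailored or peer support interventions compared to the control group will be 1-tailed". H3 is treated differently: "tests comparing both interventions together will be 2-tailed". The section describes no other between-arm test of H1–H3 and no multiplicity adjustment for the pairwise tests.

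The Sample Size Calculation section sets power at .80 and alpha at .05 and bases the calculation on the full factorial layout: "according to a mixed-plan, 3 (2 experimental groups and 1 control group) x 3 (baseline and 3- and 9-month follow-ups) design". Its conclusion is that "a total sample size of 204 participants is necessary to detect a conservative effect size of d=.20".

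**The concern.** H1–H3 are specific comparisons fixed before the data, so they are planned contrasts. The analysis section demotes them to follow-up tests after an omnibus result. Three consequences follow.

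- If the interaction is not significant, the rule as written leaves the primary hypotheses untested, however clear one comparison may be.
- H1 and H2 are to be tested in one direction, but the test in front of them is non-directional and spreads its power over four degrees of freedom. The two choices pull against each other.
- An omnibus test followed by unadjusted pairwise tests protects against false claims only when no arm works. Once one arm has an effect the interaction tends to be significant, and the remaining tests are unprotected.

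The power loss matters more because numbers are limited. The target was 204 at the end of the study. Enrolment was 234, and the article's own 60% completion assumption would leave about 140.

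**Working it through.** **Inputs from the article.** Three arms, 1:1:1; three time points; alpha .05; power .80; effect size .20; N = 204; 234 enrolled; 60% completion. Hence 234/3 = 78 per arm at baseline, and 234 × .60 ≈ 140, or about 47 per arm, at the end.

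**Assumptions not in the article.** Correlation ρ = .5 between time points, compound symmetry, equal arms, normal errors, complete data, and effects equal at both follow-ups.

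**1. The plan's own figure.** Interaction df = (3−1)(3−1) = 4. With noncentrality λ = f²·N·3/(1−ρ), df2 = 2(N−3) and f = d/2 = .10, power is .799 at N = 201 and .806 at N = 204. So 204 is reproduced as the sample size for this interaction test. At N = 234, power is .864.

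**2. What f = .10 means.** If both interventions differ from control by δ at both follow-ups, the interaction effect size is f = δ·√(2/9 × 2/9) = 2δ/9. Then f = .10 corresponds to δ = .45 SD. If .20 is read instead as the difference from control, f = .044, and the interaction is significant in only about 20% of trials at 68 per arm, 23% at 78 and 15% at 47.

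**3. H1 alone, no condition.** The difference in change from baseline has standard error √(4(1−ρ)/n). At n = 78 this is √(2/78) = .160. With δ = .4 and a one-sided 5% test, power ≈ Φ(.4/.160 − 1.645) ≈ .80.

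**4. With and without the condition (simulation, H1 at 3 months).** The last column is (ungated − gated)/(1 − gated).

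| Per arm | Effects, tailoring / peer support (SD) | Gated | Same contrast ungated | Loss (points) | Share of failures due to the gate |
|---|---|---|---|---|---|
| 78 | .4 / .4 | .68 | .80 | 12 | .12/.32 ≈ 38% |
| 78 | .4 / .2 | .58 | .80 | 22 | .22/.42 ≈ 52% |
| 47 | .4 / .4 | .43 | .62 | 19 | .19/.57 ≈ 33% |
| 78 | .2 / .2 | .16 | .35 | 19 | .19/.84 ≈ 23% |

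**5. Role of the other arm.** The interaction signal depends on the spread of the arm effects around their mean. The sum of squares for (.4, .4, 0) is .107, for (.4, 0, 0) also .107, and for (.4, .2, 0) .080. Gated power agrees: .68 and .69 in the first two cases at 78 per arm, and .58 in the third. An intermediate second arm is the bad case, not a neutral one.

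**6. Error control.** When all arms are null, the chance of at least one false rejection among six contrasts (three comparisons, two times) is about .04 with the gate and .21 without it or any adjustment. With tailoring effective (0.6 SD) and peer support null at 78 per arm, the gated plan makes a false H2 claim at one or other time in about 8–9% of trials.

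**7. Replacement procedures.** These use baseline-adjusted contrasts with Holm at two-sided .05. The three figures are the first three rows of the table.

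- Holm over H1–H3 at 3 months: .71, .68, .45, against gated .68, .58, .43.
- Holm over all six contrasts, H1 at 3 months: .63 and .37 in the first and third rows, below the gated .68 and .43.
- Holm over all six, H1 detected at either time: .78, .78, .53, against gated .74, .62, .50.

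Without baseline adjustment the result is worse. One-sided Bonferroni over six change contrasts at 68 per arm gives .11 (0.2 SD) and .47 (0.4 SD), against gated .14 and .61.

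**The case against.** The strongest defence is that an omnibus test followed by pairwise tests is conventional, that 204 is reproduced as the sample size for exactly this interaction, and that the condition is the only multiplicity protection the article describes. All three points stand. Removing the condition with nothing in its place would be worse for error control, and a six-test Holm procedure can lower power at a single time point. The match with 204 does not show adequate power for the contrasts at a 0.20 SD difference, however, because it corresponds to differences of about 0.45 SD from control.

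The article speaks of interaction terms in the plural, which could mean single coefficients. The 4 df are derived from the 3 × 3 design, not stated. Under the coefficient reading the size of the loss would differ, but the hypotheses would still be conditional and labelled post-hoc.

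A reader might infer two stronger claims.

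- *The condition is the main reason the trial could fail.* At 0.2 SD the contrast alone has only about .35 power at 78 per arm, and about 310 per arm would be needed for .80. The condition accounts for a minority of failures there. It reaches a majority only with graded effects, or with larger effects and a lenient rule that accepts success at either time point.
- *A neutral second arm would block the verdict on an effective one.* Step 5 shows no extra loss in that case.

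Nor can the advantage of the Holm alternative be credited to deleting the condition alone. It depends on baseline adjustment and on a small family.

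**Conclusion.** The point holds in a limited form. The article explicitly makes its pre-stated primary comparisons conditional on a non-directional interaction test. This decision rule is written into the text, so it is not a detail left to an analysis plan that is not shown. Under ρ = .5 and the other assumptions above, the cost is about 12 to 22 points of H1 power at one time point against the same contrast without the condition. In return the plan gets error control only under the complete null, with about 8–9% false H2 claims at either time if only the tailoring arm works. The exact sizes depend on the correlation, on attrition and on how the effects are distributed over arms and times. This should be changed, but it does not invalidate the trial, and low power for small differences remains the larger problem at 0.20 SD.

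**What to change.** - Delete the conditional sentence and the post-hoc label.
- Name tailoring − control, peer support − control and tailoring − peer support as planned, baseline-adjusted contrasts from the mixed model at 3 and 9 months. Report each one with its confidence interval whatever the interaction shows.
- State a multiplicity procedure with a small family, for example Holm over H1–H3 at 3 months as primary, followed by 9 months. Write out the rule for moving to 9 months: under a strict sequence that family opens only if all three 3-month hypotheses are rejected.
- Report the interaction F descriptively.

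The cost is a few sentences and a contrast statement in the code. Two prices should be acknowledged. The interaction loses the role on which 204 appears to rest, and 9 months ranks behind 3 months although the hypotheses name both. Because the Results section says that analysis is already under way, the change should be dated and reported with a statement of whether outcome data by arm had been seen.
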